## Abstract

**Background:**

Young adults with mobility disability (MD) are less likely to engage in regular physical activity (PA) compared with their able-bodied peers and inactive adults with a MD are more likely to report one or more chronic diseases compared to those who are physically active. Despite the vast amount of research published in the field of PA interventions over the past decades, little attention has been focused on interventions aiming to increase PA among individuals with MD. Thus, we propose to compare the effects of an eHealth program compared to a usual care supervised health program on levels of PA and other health behaviors.

**Methods:**

The current intervention will use a randomized controlled trial (RCT) design with two treatment groups (an eHealth program and a usual care supervised health program) in young adults with newly acquired MD. In total, 110 young adults (aged 18–40 years) with a MD, acquired within the past 3 years, will be recruited to participate in a 12-week intervention. The primary study outcome is accelerometer-measured time spent in moderate to vigorous PA. Secondary outcomes includes health-related quality of life, depression, stress, fitness, body composition, diet, musculoskeletal pain, motivation to exercise and work ability.

**Discussion:**

There is a lack of RCTs investigating effective ways to increase levels of PA in young adults with MD. Increased levels of PA among this physically inactive population have the potential to substantially improve health-related outcomes, possibly more so than in the general population. The trial will put strong emphasis on optimizing exercise adherence and investigating feasibility in the two treatment programs. The Ethical Review Board (EPN) at Karolinska Institutet has approved the study (2017/1206–31/1).

**Trial registration:**

International Standard Randomised Controlled Trial Number (ISRCTN), reference number ISRCTN22387524. Prospectively registered February 4, 2018

**Electronic supplementary material:**

The online version of this article (10.1186/s13063-018-2646-z) contains supplementary material, which is available to authorized users.

## Background

Approximately 10% of the Swedish population lives with a mobility disability (MD). MD is strongly associated with reduced work ability [1] and thus is a major public health concern. There are strong cross-sectional [2] and longitudinal [3] dose-response associations between physical activity (PA) and work ability, as well as health-related quality of life (HRQoL) [4]. Despite the numerous known health benefits of PA [5], young adults with MD are less likely to engage in regular PA compared with their able-bodied peers [6]. Approximately 50% of adults with MD are physically inactive, reporting little or no time spent in moderate to vigorous PA (MVPA) per day, compared to 26% of adults without MD [7]. In addition, inactive adults with a MD are 50% more likely to report one or more chronic diseases compared to those who are physically active [7].

Despite the vast amount of research published in the field of PA interventions over the past decades, little attention has been on interventions aiming to increase PA among individuals with MD [8]. Interventions focusing on PA for those with MD may be particularly important, as there is some evidence that a physically active lifestyle can provide increased health benefits for people with MD compared with the general population [9]. However, currently, PA interventions targeting individuals with MD are limited to older people [10]; therefore, there is a paucity of intervention research regarding the health benefits of PA for those with MD, especially for those who are of working age.

The few existing studies on PA and MD suggest that motivation for PA is high among individuals with MD, and that barriers to PA engagement include accessibility to tailored PA facilities, and they also have a lack of knowledge on how to engage in PA [6, 11]. In addition, enjoyment appears to be a critical individual factor for engagement in PA among these individuals [12]. A longitudinal study investigating motivation for PA, using self-determination theory, in young adults with MD indicates that autonomy, goal setting, surveillance, support and feedback are important factors for improving and maintaining healthy levels of PA [11]. Therefore, factors beyond health benefits should also be considered for helping those with a MD achieve greater levels of PA.

A recent systematic review found modest evidence for the efficacy of application interventions, that is app-based interventions, to improve the levels of PA and dietary habits for non-communicable disease prevention [13]. Given that many people have busy lifestyles, but still value access to health-behavior programs that provide advice, information, feedback and self-monitoring around the clock, app-based programs may be an important way to reach certain populations [14]. However, there is an inconsistency in the academic literature on the effects from multi-component versus eHealth app interventions on health outcomes [13]. This raises the question as to whether multi-component interventions deliver equal intervention effects compared with stand-alone app interventions.

Thus, the aim of the current randomized controlled trial (RCT) is to compare the effects of delivering an eHealth program compared to delivering a supervised health program on levels of MVPA, as well as evaluate the health-related benefits and cost-effectiveness to each program.

## Methods

### Intervention design

The current intervention will use a RCT design with two treatment groups in a sample of young adults with newly acquired MD. In this study, newly acquired MD refers to individuals who have had MD for 3 or less years. The trial will examine the efficacy of an eHealth program compared to a supervised health program, lasting for 12 weeks, on the primary (MVPA) and secondary (HRQoL, work ability, symptoms of depression, pain, stress, exercise motivation, diet, fitness, body composition and genetic/epigenetic factors) outcomes at baseline (week 0), midpoint (week 6), at the end of the intervention (week 12) and at 12 months’ post intervention follow-up to examine maintenance effects. In addition, semi-structured interviews focusing on facilitating and hindering factors associated with intervention adherence will be conducted at week 12 and at 12 months’ follow-up in a subsample of individuals from both intervention groups (illustrated in Fig. 1). All measurements, tests and information meetings will be held at a healthcare center (TWITCH Health Capital, Stockholm, Sweden). The trial will be reported according to Consolidated Standard of Reporting Trials (CONSORT) guidelines for reporting RCT designs [15] (Fig. 2). For Standard Protocol Items: Recommendations for Interventional Trials (SPIRIT) 2013 Checklist, see Additional file 1.

**Fig. 1 Fig1:**
[figure not shown]
Schematic overview of the eHealth and the supervised health intervention groups

**Fig. 2 Fig2:**
[figure not shown]
Participant flow diagram (according to Consolidated Standards of Reporting Trials (CONSORT) guidelines)

The two treatment arms are each designed to support participants to perform sustained changes in MVPA and health-related outcomes. The framework used in both intervention groups is based on the assumption that behavior-change interventions are more likely to be effective if they use intrinsic motivation strategies and are deep-rooted in health-behavior-change theory [16]. In addition, a recent meta-analysis supports the use of behavior-change techniques, including goal setting, self-monitoring and strategies for intrinsic motivation change of behavior, to promote change in healthy PA and dietary behaviors and a person-centered and autonomy supportive counseling approach in order to maintain these behaviors over time [17].

### The eHealth program

#### Short description

The eHealth program is a 12-week, standardized walking, exercise and food photography program, delivered via smartphone apps, with three face-to-face meetings with health educators (*n* = 55).

### Design

The intervention framework is based on a recent systematic review concluding that multi-component application-based interventions to improve diet, PA and sedentary behaviors can be effective [13], especially if the intervention entails app-embedded behavior-change techniques [18]. In addition, individually tailored feedback, based on the participant’s own characteristics, and advice is more likely to be effective compared with generic information about health benefits from PA [16, 19]. The Acupedo walking app will be used in the current study. The app is the number-one-ranked pedometer app at the app/google app store and comprises several behavior-change techniques, which is important when promoting PA [18]. In addition, participants will be encouraged to use an individually tailored home-based training app (three times/week) developed by the Swedish Military. This app comprises a pre-defined 12-weeks exercise program with progressively increasing exercise intensity. Both apps contain several behavior-change techniques: for example, self-monitoring and specific goal setting. Furthermore, participants will use food photography, via an app, a methodology shown to assess food intake in different environments with acceptable accuracy [20, 21]. Additionally, food photography holds promise as an intervention tool to change dietary decision-making and attitudes [22].

The intervention entails three face-to-face consultations, in groups of approximately 20 participants, held at the healthcare center. The first consultation, held at the start of the intervention (baseline), will focus on information on how to use the apps and improving motivation to increase walking and exercise, with additional discussions on goal setting and other techniques to support behavior change. The second PA consultation, held at week 6, will focus on semi-structured face-to-face interviews concentrating on facilitating and hindering factors associated with intervention adherence. Participants will review their progress towards achieving the goals set in the first meeting by discussing the information recorded on the walking app and the activity tracker. The final meeting at week 12 will focus on encouraging participants to maintain changes by reviewing goal attainment and discussing relapse prevention strategies to maintain healthy PA and other health habits. After 12 weeks, a purposive sample of participants are interviewed about their experiences of efficacy, implementation and outcomes of the app support and at 12 months with a focus on persistent changes of lifestyle.

### The supervised health program

#### Short description

The supervised health program is a 12-week standard care health program, delivered by health educators and personal trainers, including one weekly supervised exercise session (*n* = 55).

### Design

The supervised exercise program is based on the trans-theoretical and socio-cognitive models of behavior change [23]. The meetings with health educators and personal trainers within the intervention group will have a semi-structured format and a person-centered approach to ensure individualization to meet the needs of the participants with MD. To reduce the complexity of the meetings, a behavior-change model with four core behavior-change techniques (mobilizing social support for change, developing self-efficacy, goal setting and self-monitoring), that are known to be effective in supporting individuals to improve healthy activity and dietary behaviors [24] will be used. Although the focus will be on these four components, health educators and personal trainers will tailor the meetings by adding additional behavior-change techniques, such as identifying and overcoming barriers to change, and using a motivational interviewing approach where relevant. The health educators and personal trainers are experienced at adapting interventions to make them accessible to adults with MD.

Dietary advice given to the participants will follow the four-step Step-wise Weight-determined Accumulative change Plan (SWAP) model, which includes the following aspects: (1) limit sweets and snack intake to no more than 100 g/week, eaten during 1 day of the week, (2) substitute regular foods with low fat and low sugar alternatives, (3) gradually increase vegetable intake until vegetables cover half the plate at lunch and dinner and (4) reduce portion sizes by reducing equally from the carbohydrate and the fat content of the meal [25].

In addition to the dietary advice, participants will use a food photography app as described for the eHealth group. However, participants in the supervised exercise program group will also use the social media function imbedded in the app (a “locked” function made available only for this group), which enables sharing and rating of meals; thus, providing participants with social support, which has been shown to be beneficial to making behavioral changes [24].

The intervention will encompass both structured supervised and non-supervised PA including aerobic, strength, flexibility and balance training, and will be designed to be performed at fitness centers with personal trainers, one time per week with a total of 12 sessions during the intervention period. PA goals will be individualized based on each participant’s level of physical fitness (VO_2_max), and will further be modified in response to illness, injury or physical symptoms. Participants will be further encouraged to have an active lifestyle with two more weekly un-supervised exercise sessions. Participants will further be encouraged to avoid prolonged periods of uninterrupted sitting and aim at a minimum of 30 min daily walking. The weekly personal trainer supervised exercise sessions, lasting 60 min each, will target compound movements, involving large muscle groups. The exercise sessions during the first 4 weeks will aim at for a minimum of 10 min of PA at a moderate to vigorous intensity (> 60% VO_2_max). During the next 4 weeks, time in MVPA will progressively increase to 20 min per session and the last 4 weeks of the intervention will provide 30 min of MVPA per exercise session. Exercise sessions will be 60 min long throughout the intervention period. Thus, lower-intensity PA, such as balance and flexibility training, will be progressively replaced during the intervention period. The exercise sessions will be structured so that they can be generalized to the home environment; thus, possibly increasing post-intervention maintenance. Interviews with a purposive sample of participants will be performed at 12 weeks focusing on experiences of the efficacy, implementation and outcomes of the program and again at 12 months to explore persistent changes in lifestyle.

### Sample size calculation

Prior to this study, there were no objectively measured PA data from PA and exercise interventions for young adults with MD. A recent cross-sectional study with objectively measured MVPA showed an average of 11.6 min of MVPA per day (standard deviation 25.1) among individuals with MD [26]. A target between group difference of 10 min of daily MVPA, which has been shown to be a clinically relevant increase in activity, was used for the sample size calculation. For 80% power at the 5% significance level, 40 participants per group is required. To allow for a dropout rate of 20%, approximately 50 participants in each group will be required. Therefore, adopting a conservative approach, the final target sample size will be 55 participants in each treatment arm.

For the qualitative parts of this study, an estimated purposive sample is recruited. Participants are recruited until saturation of data is obtained.

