### Randomization

A block randomization procedure will be used at an individual level to ensure an equal distribution of participants between the two treatment groups. Participants will be randomized before the first baseline assessment at the healthcare center. The SAS Proc Plan (SAS Institute Inc., Cary, NC, USA) will be used for the randomization process. The block size will not be stated in the protocol so that the investigators are blind to the block size. Thus, limiting potential risk for selection bias.

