## Statistical analyses

### Primary and secondary outcome measures

The primary study outcome, difference in levels of MVPA at 12 weeks between the two treatment groups, will be tested on an intention-to-treat approach, with all participants analyzed in the group to which they were randomized, using a two-tailed 0.05 significance level. We will further conduct per-protocol analysis to evaluate the effect on levels of MVPA at 12 weeks among those who followed the study protocols. Both intention-to-treat and per protocol analyses will be performed on differences in the main and secondary outcomes between the two groups at 12-week and 12-month follow-ups. Mixed-effects regression models will be used for analyses accounting for baseline levels of MVPA and possible clustering of the randomized groups. Similar regression models will be fitted for secondary outcomes. Data will be presented as interclass correlation coefficients, adjusted mean differences (95% confidence interval) and corresponding *p* values. For the primary outcome, within- and between-group changes will also be calculated from a repeated-measures mixed-effects model.

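### The 40 per group stated for 80% power does not follow from the only inputs printed (SD 25.1, difference 10 min/day, two-sided 5%), which call for about 100 per group in an unadjusted comparison

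*Protocol article*

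**What the plan says.** All of the following is in the protocol article.

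- **Variability** (Sample size calculation): a cross-sectional study "showed an average of 11.6 min of MVPA per day (standard deviation 25.1) among individuals with MD". This is the only standard deviation of daily MVPA in the document.
- **Effect** (same section): "A target between group difference of 10 min of daily MVPA", described as clinically relevant and as having been used in the calculation.
- **Result** (same section): "For 80% power at the 5% significance level, 40 participants per group is required".
- **Dropout and final size** (same section): "To allow for a dropout rate of 20%, approximately 50 participants in each group will be required"; then, described as conservative, "the final target sample size will be 55 participants in each treatment arm".
- **Test** (Primary and secondary outcome measures): the between-group difference in MVPA at 12 weeks is tested "using a two-tailed 0.05 significance level". Mixed-effects models are planned that account for baseline MVPA.
- **Allocation** (Randomization): blocks are used "to ensure an equal distribution of participants between the two treatment groups", so 1:1.

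The document gives no SD of change, no residual SD and no correlation between baseline and week-12 MVPA.

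**The concern.** A difference of 10 against an SD of 25.1 is a standardised difference of about 0.40. Forty per group is far too few to detect that with 80% power in a plain two-group comparison. The paragraph is the whole justification for the size of the trial and it concerns the primary test. A reader who takes the 80% at face value, and sees 55 per arm called conservative, would treat a null result as coming from an adequately powered trial. That matters here because the Background asks whether the two kinds of program deliver equal effects, so a null result could be misread as evidence that they do.

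**Working it through.** **Inputs.** Difference 10 min/day, SD 25.1, power 80%, dropout 20% and 55 per arm (Sample size calculation); two-sided alpha 0.05 (Primary and secondary outcome measures); 1:1 allocation (Randomization). The correlation r between baseline and week-12 MVPA is not in the document. Every value of r below is an assumption.

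**1. Trying to reproduce 40.** For two independent means:

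n per group = 2 × (1.960 + 0.842)² × SD² / difference² = 2 × 7.849 × 630.01 / 100 = 98.9

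This gives 99 per group, or 100 with the t distribution (99.9). The stated 40 is too low by a factor of about 2.5. Other formulas do not recover it:

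| Formula with SD 25.1, difference 10 | n |
|---|---|
| Two-sample, two-sided | 99 (normal), 100 (t) |
| Two-sample, one-sided | 78 (normal), 79 (t) |
| One-sample, two-sided | 50 (normal), 52 (t) |
| One-sample, one-sided | 39 (normal) |

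Only the last comes close, and it matches neither the two-group comparison nor the two-tailed test.

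**2. The dropout step.** 40 / (1 − 0.20) = 50. This is correct, so the problem lies in the 40.

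**3. What would give 40.**

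- A smaller SD: SD = 10 × √(40/2) / 2.802 = 15.96 by the normal formula, or 15.8 by t. "About 15.8" is used below.
- Baseline adjustment, where the residual SD is 25.1 × √(1 − r²): r = √(1 − (15.96/25.1)²) = 0.77.
- A change score, where the SD is 25.1 × √(2(1 − r)): r = 1 − (15.96/25.1)²/2 = 0.80.

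None of these values is stated.

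**4. Power for a true difference of 10 min/day** (noncentral t, two-sided 5%). Evaluable per arm after dropout: 55 × 0.80 = 44. Baseline adjustment uses SD 25.1 × √(1 − r²).

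| Assumed r | n per group for 80% power | Power at 44 per arm | Power at 55 per arm |
|---|---|---|---|
| Unadjusted | 100 | 46% | 54% |
| 0.5 | 75 | 57% | 67% |
| 0.6 | 64 | 64% | 74% |
| 0.7 | 51 | 73% | 83% |
| 0.75 | 44 | 80% | 88% |

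The second column is rounded; the normal approximation gives powers within about one percentage point of these. At 40 per arm, unadjusted power is 42%.

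**5. Detectable difference.** With 80% power, unadjusted, at 44 per arm: 25.1 × √(2/44) × 2.802 = 15.0 min/day, or 15.2 with the t distribution.

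**The case against.** The strongest reply is that the unadjusted figures do not describe the planned test. The protocol adjusts for baseline MVPA, so the relevant quantity is a residual SD, which may be well below 25.1. The text ties the 10-minute difference to the calculation but never says outright that 25.1 was the SD entered. A journal article also condenses the full protocol, which may record another SD or a correlation.

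Part of this stands. The true power of the planned analysis depends on a correlation the document does not give, so 46% cannot be presented as the power of the trial. A reader might also infer that a non-significant result is more likely than not even if the target difference is real. The document does not support that as a general statement. It holds for the unadjusted comparison with 44 per arm. It fails if all 55 per arm are evaluable (54% unadjusted), and it fails under the planned adjustment at 44 per arm for r = 0.5 and above (57% or more).

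The reply does not rescue the paragraph. The SD of 25.1 is the only one printed and comes directly before the calculation. Reaching 40 needs an SD of about 15.8, or r of about 0.77 with adjustment or 0.8 with change scores, and a value that decides the sample size has to appear with it. The section itself says that no objectively measured activity data from interventions existed in this population, so the source of such a value is not apparent. Nor is this a complaint about something left to a fuller document: the inputs and the result printed together do not agree.

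It is also fair to say that 55 is cautious relative to 50. It is not cautious relative to what the printed inputs require.

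**Conclusion.** The point holds: the sample size statement is wrong as written. The printed inputs need about 100 per group for an unadjusted two-sided comparison, against 40 stated.

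With SD 25.1 and a true difference of 10 min/day, 44 evaluable per arm gives about 46% power unadjusted, and about 57% to 73% with baseline adjustment for r between 0.5 and 0.7. The stated 80% is reached only at about r = 0.75. With no losses the figures are 54% and about 67% to 83%.

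That 40 does not follow from the printed inputs is certain. The power of the planned analysis is not: it rests on the assumed r, on 25.1 applying to this population, and on the actual dropout.

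**What to change.** Keep 110 participants and correct the Sample size calculation paragraph in one of two ways.

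1. If a smaller SD or a baseline correlation was used to reach 40, state it, its source and the analysis it belongs to (SD about 15.8; r about 0.77 with baseline adjustment; or r about 0.8 for change scores).
2. Otherwise restate the power. For SD 25.1 and 10 min/day at 44 evaluable per arm, it is about 46% unadjusted and about 57%, 64% and 73% with baseline adjustment at r = 0.5, 0.6 and 0.7, reaching 80% at about r = 0.75. With all 55 per arm evaluable, it is 54% unadjusted and about 67% to 83% for r = 0.5 to 0.7. Add the difference detectable with 80% power, about 15 min/day unadjusted at 44 per arm.

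Drop the description of 55 per arm as conservative unless the first option applies and the assumption is justified.

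The cost is one rewritten paragraph and, under the second option, a less favourable power statement. No extra participants and no change to trial conduct are needed.
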